## Abstract

**Background:**

Hip fractures constitute an economic burden on healthcare resources. Most persons with a hip fracture undergo surgery. As morbidity and mortality rates are high, perioperative care leaves room for improvement. Improvement can be achieved if it is organized in comprehensive care pathways, but the effectiveness of these pathways is not yet clear. Hence the objective of this study is to compare the clinical effectiveness of a comprehensive care pathway with care as usual on self-reported limitations in Activities of Daily Living.

**Methods/Design:**

A controlled trial will be conducted in which the comprehensive care pathway of University Medical Center Groningen will be compared with care as usual in two other, nonacademic, hospitals. In this trial, propensity scores will be used to adjust for differences at baseline between the intervention and control group. Propensity scores can be used in intervention studies where a classical randomized controlled trial is not feasible. Patients aged 60 years and older will be included. The hypothesis is that 15% more patients at University Medical Center Groningen compared with patients in the care-as-usual condition will have recovered at least as well at 6 months follow-up to pre-fracture levels for Activities of Daily Living.

**Discussion:**

This study will yield new knowledge with respect to the clinical effectiveness of a comprehensive care pathway for the treatment of hip fractures. This is relevant because of the growing incidence of hip fractures and the consequent massive burden on the healthcare system. Additionally, this study will contribute to the growing knowledge of the application of propensity scores, a relatively novel statistical technique to simulate a randomized controlled trial in studies where it is not possible or difficult to execute this kind of design.

**Trial registration:**

Nederlands Trial Register NTR3171

## Background

Hip fractures constitute an economic burden on healthcare resources that will continue to rise. Approximately 17,000 older persons sustain a hip fracture in the Netherlands every year [1]. Costs of treatment, rehabilitation and home care are considerable (nearly EUR 400 million per year). Regardless of the costs, hip fractures have a negative effect on activities of daily living and quality of life. One year after the fracture, less than 50% of patients have fully recovered [2]. Most persons with a fracture undergo surgery. However, perioperative care in hip fracture patients leaves much room for improvement, as convalescence after surgery is often hindered by complications. As a consequence, hip fracture is associated with high mortality and considerable loss of function [3]. Complications may occur in many organ systems and require the involvement of various medical specialties. In theory, the involvement of many specialties should guarantee the best possible treatment, yet in practice the care tends to be rather fragmented. Therefore, it is generally felt that perioperative care can be improved if care is organized in comprehensive care pathways. Aim of care pathways is to optimize care during the entire process of surgery and rehabilitation. The effectiveness of care pathways for persons with a hip fracture was investigated in studies that show a tendency for the pathways being more effective than usual care [4-6]. However, the extensiveness of these care pathways differs and most care pathways deal with only one or a few aspects of the care (e.g. the postoperative rehabilitation in hospital care).

To overcome this shortcoming a comprehensive care pathway for the treatment of patients with a hip fracture was developed at University Medical Center Groningen (UMCG). In this pathway the care is described from arrival at the emergency room until discharge from the nursing home. The objective of this study is to determine the clinical effectiveness of this pathway. To that end, a controlled trial will be conducted in which the new comprehensive care pathway of UMCG will be compared with care as usual at Martini Hospital Groningen (MHG) and Ommelander Hospital in Winschoten (OHW). It is hypothesized that 15% more patients treated in the new comprehensive care pathway compared with patients in the care-as-usual condition will have recovered at least as well at 6 months follow-up to pre-fracture levels in terms of Activities of Daily Living (ADL). As a randomized controlled trial (RCT) is not feasible, propensity scores will be used to adjust for differences at baseline between the intervention and control group.

## Methods/Design

### Study design

A controlled intervention will be executed to compare the clinical effectiveness of the new comprehensive care pathway for the treatment of hip fractures with care as usual. Initially a RCT was planned for this purpose. A RCT within one hospital was not justified, because patients are clustered in one ward with a dedicated team. To treat patients with the same diagnosis in two different ways, it was decided to compare patients to be treated with the care pathway at UMCG with care as usual in other hospitals in the Groningen area. To assess if such a RCT was feasible a pilot study was done to test the randomization process. This showed that randomization on the spot performed by ambulance personnel was not feasible. Of the 154 elderly patients with a hip fracture eligible for randomization, only 14 (9%) gave informed consent. It was therefore decided to perform a controlled trial with propensity score adjustment. Propensity scores can be used to adjust for differences at baseline between the intervention and control group in situations in which a classical RCT is not feasible.

The study has been approved by the Medical Ethical Committee of University Medical Center Groningen and is registered in the Dutch trial register (NTR3171).

### Setting

The study will be executed in three hospitals in the northeastern part of the Netherlands. UMCG is a tertiary university hospital, located in the city center of Groningen. Martini Hospital Groningen (MHG) is a large teaching hospital in the southern part of the city and Ommelander Hospital Winschoten (OHW) is a smaller, rurally-located hospital situated in the town of Winschoten, 40 km east of the city of Groningen. Although these three hospitals differ in certain aspects such as size, medical specialty services and educational assignments, they all offer the same standard care for patients with a hip fracture. In the Netherlands, standard care for patients with a hip fracture is based on a national professional guideline [7]. Therefore, it can be assumed that the usual care in the three hospitals prior to the intervention study is comparable. Patients are taken to one of the hospitals on basis of proximity and availability, not based on the characteristics of the hospital. Especially with respect to the UMCG, it must be mentioned that this hospital does not only provide academic or tertiary care but due to its position as one of the few hospitals in the Northern Netherlands, also provides general (secondary) medical and surgical care. Patients admitted to UMCG for treatment will be treated in the new comprehensive care pathway. Patients transported to Martini Hospital Groningen and Ommelander Hospital Winschoten will receive care as usual.

### Participants

Patients aged 60 years and older with a hip fracture defined as a femoral neck fracture (dislocated or not dislocated) and pertrochanteric and intertrochanteric fractures (AO Comprehensive Classification 31.A.1; 31.A.2; 31.A.3) will be included. Exclusion criteria are patients with multi-trauma injuries (thoracic and/or abdominal) and patients who are not able to fill in questionnaires, who are not able to understand the Dutch language, or who are not able to give informed consent. Patients with mild dementia, who do not fully understand the study, but are able to fill in the questionnaires with the help of close relatives can be included when these close relatives give their informed consent and the patient agrees.

### Intervention

In the new comprehensive care pathway of UMCG the treatment and the role of every participant is described from arrival at the emergency room until discharge from the nursing home. This new treatment protocol comprises multidisciplinary cooperation between trauma surgeon, orthopedic surgeon, anesthesiologist and geriatrician, a preoperative workup protocol, a fixed moment of surgery and a postoperative protocol in close collaboration with the physical therapist and nursing home physician. The comprehensive care pathway does not end with discharge from the hospital. The core elements of the pathway are:

– A shared preoperative planning protocol for both the departments of orthopedics and traumatology.

– A perioperative anesthesiological risk assessment in the emergency room already, instead of later on the ward.

– Enrolment of the patients for surgery at a fixed time in the emergency operating rooms (OR). Each morning at 8:00 AM an emergency room with plenum is available for such a patient if necessary. An experienced surgeon and OR team are also available.

– Because of the fixed time of surgery, 8:00 AM on the day after admission, there is allowance for patients to eat until midnight — eight hours before surgery — causing minimal discomfort.

– A uniform treatment protocol for both surgery teams of the departments of orthopedics and traumatology.

– Clustering of all hip fracture patients on one nursing ward in order to use the experience and knowledge of the nursing staff and consequently improve the quality of care for the patient, with extra attention for care of elderly patients (early start of rehabilitation, adequate nutrition, prevention of pressure ulcers and delirium).

– Daily visits by the geriatric team during the stay at the nursing ward.

– Early initiation of standard discharge procedures. Upon arrival at the hospital the patient is already registered for transfer to a nursing home.

– Planned capacity at the nursing homes for an efficient transfer of patients. In addition, the nursing home physician is able to view the data of patients with hip fracture in the data management systems of UMCG. Since this doctor handles the admissions, he/she can view the progress of the patients and anticipate their arrival.

– Patients are seen at a special outpatient clinic for hip fracture patients. The last visit is planned 6 months after the operation. Special attention is paid to functioning in daily living activities.

### Care as usual

At Martini Hospital Groningen and Ommelander Hospital Winschoten, patients will receive care as usual. This comprises the following:

– The diagnosis of hip fracture is established by assessment and X-ray at the emergency room.

– Depending on the general surgeon or orthopedic surgeon on call (fixed rotation schedule), a decision about the operative treatment is made. The choice for a specific surgical procedure depends on the surgeon on call and the local trauma protocol.

– The patient will be admitted to one of the surgical or orthopedic wards.

– Preoperatively an anesthesiologist will examine the patient and assess available medical information.

– The patient will be treated according to local hospital protocols and techniques.

– From the day of admission specific risk factors (malnutrition, decubitus risk, delirium) are categorized in a standardized way using a scoring list and specialized staff.

– A geriatrician is not involved by default.

– Postoperatively the patient will be mobilized, and physical therapy is arranged for.

– There are some agreements with nursing homes for transfer to a rehabilitation facility or retirement center.

### Measurements

Measurements will be taken preoperatively, perioperatively, and at 6 weeks and 3 and 6 months after surgery. Preoperative demographic data, preoperative diagnosis, height, weight, Body Mass Index and ASA classification will be recorded. Hip fractures will be classified as femoral neck fractures and pertrochanteric or intertrochanteric fractures. Average surgical time, intraoperative blood loss, in-hospital transfusion rate and complications will be recorded perioperatively. Mortality will also be recorded.

Self-reported limitations in ADL will be measured with the Katz index and Lawton Instrumental Activities of Daily Living (IADL) scoring list [8,9]. The Katz index is based on an evaluation of the functional dependence or independence of patients in bathing, dressing, going to the toilet, transferring, continence and feeding. ADL index A indicates independence in all six functions, index B independence in all but one of the six functions. Indexes C–G indicate dependence in bathing and at least one additional function. The IADL scoring list is an evaluation of the abilities of patients in eight activities: using the telephone and transportation, shopping, preparing food, housekeeping and laundry, responsibility for their own medications and handling finances. On the basis of the score patients are divided into different categories that state something about their degree of independence.

Health-related quality of life will be measured using the EQ-5D (EQ-5D™ Dutch© 1987 Euroquol Group). The EQ-5D has five dimensions: mobility, self-care, usual activities, pain/discomfort, and anxiety/depression. Each dimension is divided into three degrees of severity: no problem, some problems, and major problems. Actual quality of life must also be signed on the EQ VAS scale. The Katz index and IADL scoring list are measured at the hospital (to determine the situation before the fracture) and at 6 weeks and 6 months after the operation. The EQ-5D will be assessed on the same occasions and at 3 months after the operation.

At the outpatient clinic, at 6 weeks and 6 months after the operation, fracture consolidation, complications and Harris Hip Score will be assessed [10]. The Harris Hip Score (HHS) is a validated functional hip score that measures four items: pain, function, range of motion and deformity, in that order of importance. A score between 90 and 100 points means an excellent outcome, a score lower than 70 means a poor outcome. Six months after the operation the living and independence situation (percentage of people living in their own home again) of the patient is evaluated.

### Sample size

The power calculation is based on the hypothesis that 15% more patients treated with the new comprehensive care pathway compared with patients in the care-as-usual condition will have recovered at least as well at 6 months follow-up to pre-fracture levels in terms of ADL as measured with the Katz index. In order to detect this 15% difference with 80% power at a significance level of 0.05 (one-sided), 130 patients are needed in the new comprehensive care pathway condition and 130 in the usual care condition. Since a comparison will be made between UMCG and MHG as well as between UMCG and OHW, 130 patients will be included in MHG and 130 in OHW. Taking into account an expected drop out-rate of 15% a total of 450 patients have to be included.

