### Statistical analyses

Statistical analysis will be performed with IBM SPSS Statistics 19.0 (IBM, Amonk, NY). As conventional randomization is not feasible in this patient group, propensity score adjustment will be applied. Propensity scores, or the likelihood to be in the treatment condition or control condition, will be estimated with the following (pre-fracture) variables: age, gender, marital status, living situation, functional status, co morbidity, cognitive function, number of medications, need for home care, need for day care. Propensity scores will be used as an independent variable in the multivariate analysis.

Descriptive statistics will be used to describe the main characteristics of the population. For comparison between UMCG and MHG and OHW a multivariate analysis of variance (MANOVA) will be applied. The Katz index, Lawton Instrumental Activities of Daily Living (IADL) scoring list, the EQ-5D and HHS will be included as dependent variables and hospital and the propensity score as independent variables. A p-value lower than 0.05 will be considered as statistically significant.

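### The sample size rests on a one-sided 5% test, but the only planned test is a non-directional MANOVA at p<0.05; on a two-sided 5% test of Katz recovery, 130 v 130 gives about 68-71% power, not 80%

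*Protocol article*

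**What the plan says.** The Sample size section of the protocol article sets the target: "The power calculation is based on the hypothesis that 15% more patients treated with the new comprehensive care pathway" will have regained their pre-fracture ADL level on the Katz index at 6 months. It continues: "In order to detect this 15% difference with 80% power at a significance level of 0.05 (one-sided), 130 patients are needed" in each condition. The design has two pairwise comparisons, each of that size: "Since a comparison will be made between UMCG and MHG as well as between UMCG and OHW", 130 patients are planned in each usual-care hospital. With 15% drop-out the total is put at 450.

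The Statistical analyses section plans a MANOVA. The dependent variables are the Katz index, the Lawton IADL list, the EQ-5D and the Harris Hip Score; hospital and propensity score are the independent variables. The decision rule is: "A p-value lower than 0.05 will be considered as statistically significant". No one-sided qualifier appears there, and no directional contrast is named.

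**The concern.** One section fixes a one-sided alpha of 0.05. The other fixes a non-directional test at the same nominal 0.05. A MANOVA statistic becomes large whether the pathway does better or worse. For a contrast of two hospitals on one outcome, p<0.05 from such a test is a two-sided 5% test, with 2.5% in the favourable direction. The stated 80% therefore describes a different test from the one planned.

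Two things are at stake.

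- A null result would be read against 80% power. On a two-sided test of Katz recovery, a true 15-point benefit would be missed about 3 times in 10, not 2 in 10.
- Two conventions in one plan leave room to choose after the data are seen. For a test of Katz recovery, a favourable result with a two-sided p between 0.05 and 0.10 succeeds under the Sample size section's rule and fails under a non-directional 0.05 rule.

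**Working it through.** **Inputs from the article**

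- Sample size: difference of 15%, power 80%, one-sided alpha 0.05, 130 v 130 per comparison, total 450 with 15% drop-out.
- Statistical analyses: MANOVA, p<0.05.

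**Assumptions**

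- The 15% is an absolute difference. A relative 15% would need 208 to 841 per group one-sided at control rates from 70% down to 40%, far from 130.
- The usual-care recovery rate at 6 months is not stated. The nearest figure is in the Background: "One year after the fracture, less than 50% of patients have fully recovered". I scan 30-55%.

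**Formulas** (two proportions p1 and p2, mean p̄, d = 0.15, normal approximation, no continuity correction)

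- n per group = [z_α √(2p̄(1−p̄)) + z_0.80 √(p1(1−p1)+p2(1−p2))]² / d²
- Power = Φ([d − z_α √(2p̄(1−p̄)/n)] / √([p1(1−p1)+p2(1−p2)]/n))
- z_α is 1.645 one-sided and 1.960 two-sided; z_0.80 is 0.842.

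**Step 1: reproduce 130, then change only the sidedness**

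| Usual care v pathway | n, one-sided | n, two-sided | Power at 130 v 130, one-sided | Power at 130 v 130, two-sided |
|---|---|---|---|---|
| 30% v 45% (same for 55% v 70%) | 128 | 163 | 80.6% | 70.7% |
| 35% v 50% (same for 50% v 65%) | 134 | 170 | 79.1% | 68.9% |
| 40% v 55% (same for 45% v 60%) | 136 | 173 | 78.4% | 68.0% |
| 42.5% v 57.5% | 137 | 174 | 78.3% | 67.9% |

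The stated 130 lies between 128 and 134, so it reproduces as a one-sided number. Over this range a two-sided test needs 163-174 per group.

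Worked example, 35% v 50% at n = 130: √(2×0.425×0.575/130) = 0.0613 and √((0.2275+0.25)/130) = 0.0606. One-sided: (0.15 − 1.645×0.0613)/0.0606 = 0.81, power 79.1%. Two-sided: (0.15 − 1.960×0.0613)/0.0606 = 0.49, power 68.9%.

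**Step 2: sensitivity to the formula**

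With unpooled variance, n = (z_α + z_0.80)² [p1(1−p1)+p2(1−p2)]/d². This gives 126-134 one-sided and 160-171 two-sided; power at 130 v 130 is 78.9-81.2% one-sided and 68.7-71.5% two-sided. The picture is the same.

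**Step 3: a check that needs no control rate**

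If one-sided power is exactly 80%, the standardised effect is 1.645 + 0.842 = 2.487. Two-sided power is then Φ(2.487 − 1.960) = Φ(0.527), about 70.1%. The loss of about 10 points comes from sidedness alone.

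**Step 4: both usual-care hospitals combined, two-sided 0.05**

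- With 130 v 260 evaluable: 80.1-82.9% (pooled variance), 80.5-84.1% (unpooled).
- 450 × 0.85 = 382.5 evaluable, or 127.5 per hospital if recruitment is equal, hence 127.5 v 255: 79.3-82.2% (pooled), 79.8-83.4% (unpooled).

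These figures ignore any precision lost to propensity adjustment.

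**The case against.** The sample size arithmetic is not wrong: 130 follows from a one-sided alpha that is openly declared. The hypothesis is directional, and a disclosed one-sided test of it is legitimate. The article never uses the word two-sided, and it condenses a fuller document that could specify a directional contrast on the Katz endpoint. All of this stands, and it makes the defect an inconsistency between two sections, not a calculation error. It does not remove the defect, because the article does fix an analysis, and that analysis has no direction.

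A reader might infer more than the article supports, in three ways.

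- **That the planned analysis has 68-71% power.** That figure is for a two-sided comparison of the proportion regaining their pre-fracture Katz level. The MANOVA takes four outcomes together, and the article gives no standard deviations, correlations or effects for the other three, so its power cannot be derived. Aligning alpha alone does not close the gap between a binary recovery endpoint and a four-outcome analysis.
- **That one-sided testing is itself an error because it cannot report harm.** That is a general preference between test types. The fault here is only that the two sections do not match.
- **That combining the usual-care hospitals guarantees at least 80% power by a change of wording.** With the 450 planned patients and 15% drop-out, power falls just short of 80% at some recovery rates in the assumed range. It would also combine a large teaching hospital with a smaller rural one (Setting section), which changes the comparisons that the Sample size section states.

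**Conclusion.** The concern holds as an inconsistency between the Sample size and Statistical analyses sections. The 80% applies to a one-sided 5% test of Katz recovery; the only planned test is non-directional at p<0.05. At two-sided 0.05, 130 v 130 gives about 68-71% power on Katz recovery, against 78-81% one-sided under the same assumptions. The range rests on an assumed usual-care recovery of 30-55%, an absolute gain of 15 points and a two-proportion normal approximation. The drop of about 10 points does not depend on the recovery rate within that approximation. No power can be given for the MANOVA itself. It should be corrected, because 80% is the figure against which the trial's result will be read, and the correction is cheap.

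**What to change.** Use one alpha and one sidedness in both sections.

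- **Preferred:** state two-sided 0.05 in both, and restate the power of each single-hospital comparison on Katz recovery as about 68-71% with 130 v 130 evaluable, giving the assumed usual-care recovery rate.
- **Alternative:** keep one-sided 0.05, and name in the Statistical analyses section a directional test of Katz recovery at 6 months to which the 80% applies.
- **Optional, with two-sided 0.05:** name UMCG v both usual-care hospitals combined as the primary comparison, with power given as about 80% (79-83% with 127.5 v 255 evaluable). The sponsor would have to adopt this openly as a change to the stated pairwise comparisons.

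None of these needs extra patients. The preferred option costs a less favourable stated power, the alternative costs an added test in the analysis section, and the optional step changes the primary question. Keeping 80% for each pairwise comparison at two-sided 0.05 would instead take about 160-174 evaluable patients per hospital, depending on the formula.

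### The 15% drop-out allowance is too small: 450 enrolled leaves about 127 evaluable patients per hospital, not the 130 the sample size section requires

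*Protocol article*

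**What the plan says.** The statement is in the protocol article, Methods/Design, Sample size. For 80% power at a one-sided 0.05 level to detect a 15% difference in recovery on the Katz index at 6 months, "130 patients are needed in the new comprehensive care pathway condition and 130 in the usual care condition". The section then extends this to a third group: "Since a comparison will be made between UMCG and MHG as well as between UMCG and OHW, 130 patients will be included in MHG and" the same number in OHW. The requirement is therefore 130 in each of UMCG, MHG and OHW.

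The drop-out allowance comes last: "Taking into account an expected drop out-rate of 15% a total of 450 patients have to be included". The section gives no inflation formula and does not say how the 450 are divided between the hospitals.

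**The concern.** The allowance has one purpose, which is to leave the required number of patients with a 6-month outcome after the expected losses. Drop-out is a fraction of those enrolled, so the required number must be divided by the fraction retained (1 - 0.15). Adding 15% to the required number is a different operation and always gives a smaller total. The stated 450 looks like the result of the second operation.

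If so, a trial that recruits exactly to plan and loses exactly the expected share ends below its own target, and the power statement no longer matches the number enrolled.

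**Working it through.** **Inputs, all from the Sample size section**

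- Required per hospital: 130
- Hospitals: 3, so 3 x 130 = 390 required in total
- Expected drop-out: 15%
- Stated total to include: 450

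**Reproducing the stated total**

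- Multiplying per hospital: 130 x 1.15 = 149.5, rounded up to 150; 3 x 150 = 450. This matches exactly.
- Multiplying the total: 390 x 1.15 = 448.5, rounded up to 449. This is close but not exact.
- Dividing per hospital: 130/0.85 = 152.9, rounded up to 153; 3 x 153 = 459.
- Dividing the total: 390/0.85 = 458.8, rounded up to 459.

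Only multiplication per hospital gives 450 exactly.

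**What 450 delivers**

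- Evaluable in total: 450 x 0.85 = 382.5, against 390 required; shortfall 7.5.
- Evaluable per hospital with equal enrolment: 382.5/3 = 127.5, against 130; shortfall 2.5.
- Drop-out at which 450 would still leave 390: 1 - 390/450 = 13.3%, below the stated 15%.
- Extra enrolment needed: 459 - 450 = 9 patients, 3 per hospital; 9/450 = 2.0%.

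**Effect on power**

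The section gives no recovery rate under usual care, so a range is assumed. The 15% is read as 15 percentage points. The test is one-sided at 0.05 with n per group, control rate p1, p2 = p1 + 0.15 and p the mean of the two rates:

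power = Φ{ [0.15√n - 1.645√(2p(1-p))] / √(p1(1-p1) + p2(1-p2)) }

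Example at p1 = 0.425, p2 = 0.575, p = 0.5:

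- 1.645 x √0.5 = 1.163, and √(0.2444 + 0.2444) = 0.699
- n = 130: (1.710 - 1.163)/0.699 = 0.783, power 78.3%
- n = 127.5: (1.694 - 1.163)/0.699 = 0.759, power 77.6%

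| Assumed control rate | n per group for 80% power | Power at 130 | Power at 127.5 |
|---|---|---|---|
| 30% or 55% | 128 | 80.6% | 79.9% |
| 35% or 50% | 134 | 79.1% | 78.4% |
| 40% or 45% | 136 | 78.4% | 77.7% |
| 42.5% | 137 | 78.3% | 77.6% |

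The loss is about 0.7 points throughout. An unpooled variance gives slightly higher levels at 127.5 (78.2% to 79.0% for control rates of 35% to 50%), and the loss from 130 to 127.5 is again about 0.7 points.

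**The case against.** The strongest objection is that the effect is negligible beside the uncertainty in the inputs. The 15% is a round planning figure, and 450 would suffice at 13.3%. The 130 itself depends on an unstated control rate: for control rates of 30% to 55% the requirement runs from 128 to 137 per group, a wider spread than the 2.5 patients at issue. In the middle of that range 130 per group already gives less than 80% power, so most of any gap from 80% there is not due to the drop-out allowance. If the two control hospitals were taken together (127.5 against 255, which is not the stated basis for power), power would be about 87% to 91% for control rates of 25% to 60%. All of this stands, and it limits the weight of the point.

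Two further objections are that the multiplication by 1.15 is inferred and that equal enrolment is implied but not stated. Both are true, but neither removes the shortfall. A 15% loss from 450 leaves 382.5 however 450 was obtained. Because 382.5 is below 390, at least one hospital must fall below 130 under any split.

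One might also ask whether the 130 already includes drop-out. The wording does not allow this: 130 is the number needed for the stated power, and drop-out is introduced afterwards to reach 450. Nor is this a detail left to a fuller document, because the required number, the drop-out rate and the total are all given in the article and conflict.

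**Conclusion.** The concern holds. On the article's own figures, 450 enrolled does not leave 130 evaluable patients in each of three hospitals after 15% drop-out; the consistent total is 459.

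The error is minor: 2% of enrolment and less than one percentage point of power in each of the two hospital comparisons. It changes no design choice or analysis. The shortfall in the total rests only on the stated 130, three hospitals and 15%. The figure of 127.5 per hospital also assumes equal enrolment, and the power figures assume control rates of 30% to 55% and an absolute difference of 15 points.

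**What to change.** Either of two corrections to the Sample size section resolves it:

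- Replace 450 with 459 (153 per hospital) and state that the required number was divided by 0.85. This costs 9 more patients, 3 per hospital.
- If recruitment is fixed at 450, keep the total but state that it is expected to yield about 382 evaluable patients, about 127 per hospital, and restate the power for that number together with the control recovery rate assumed. This costs a sentence and no patients.

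In either case the section should state the intended enrolment per hospital, so that the total can be checked against the 130 required in each.
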